#### Missing Data

Any missing data for the primary outcome, PEQD, will be addressed using multiple imputation. The imputation model will incorporate both baseline and post-randomization outcome variables to ensure valid inferences under the assumption that data are missing at random. Assessments of the variable distributions, such as linearity and skewness, will be conducted to inform the selection of the multiple imputation approach. There will be no planned imputation of any secondary or tertiary outcomes.

#### Statistical Programming

All analyses will be completed using the R statistical programming software (R Foundation for Statistical Computing) [25], and Subversion (Apache Software Foundation) version control will be used to ensure reproducibility and code integrity through the tracking of code changes.

## Results

Study recruitment began in April 2023 and was completed in February 2024, with 139 participants successfully enrolled. Data collection concluded on May 26, 2025, and results are expected in the spring of 2026.

The 139 recruited participants are fewer than our initial sample size of 222 and will influence our power to detect an improvement in patient satisfaction. The impact of the smaller recruited sample size will lower our statistical power from 90% to 80% to detect a 10-point difference, with adjustment of our initial assumption from the 15% expected loss to follow-up to instead having no expected loss-to-follow-up, with the imputation of missing outcome values. Another perspective is that we would retain 90% power to detect a 10-point difference in the outcome if we adjust our SD estimate (range/6 = 16.7) to reflect those recommended by Hozo et al [24] for larger sample sizes (n>70). Even with lower recruitment numbers, we anticipate our evaluation to remain well-powered (>80%) to detect a 10-point improvement in patient satisfaction.

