### Statistical Plan

#### Sample Size

The sample size was estimated using the *power_oneway_ancova*() function from the *Superpower* package in R (R Foundation for Statistical Computing) [23]. Assuming a baseline PEQD patient satisfaction score of 80/100, a SD of 20.8 ([range/4+range/6] ÷ 2; modified from Hozo et al [24]), an equal 1:1 random allocation per study arm, and a 5% type-I error rate, a sample size of 94 participants per treatment group would provide 90% power to detect a 10% absolute between-group improvement in patient satisfaction. Furthermore, assuming 15% of participants are lost to follow-up, the required sample size was inflated to 111 per group, for a total sample size of 222.

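### The 80% power quoted for 139 participants counts imputed 8-month PEQD scores as observed; at SD 20.8 it needs essentially complete data

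*Protocol article*

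**What the plan says.** The Sample Size section takes "Assuming a baseline PEQD patient satisfaction score of 80/100, a SD of 20.8", "an equal 1:1 random allocation per study arm, and a 5% type-I error rate", and concludes that "94 participants per treatment group would provide 90% power to detect a 10% absolute between-group improvement in patient satisfaction". It then allows for attrition: "assuming 15% of participants are lost to follow-up, the required sample size was inflated to 111 per group, for a total sample size of 222".

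The Results section reports that recruitment closed "with 139 participants successfully enrolled". It puts the resulting power at 80% for a 10-point difference. To reach that figure it gives up the 15% loss in favour of "instead having no expected loss-to-follow-up, with the imputation of missing outcome values". As a second view, it says 90% power is kept if the SD is taken as 16.7 (range/6). It concludes: "Even with lower recruitment numbers, we anticipate our evaluation to remain well-powered (>80%) to detect a 10-point improvement in patient satisfaction".

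The Missing Data section plans multiple imputation of the PEQD under missing at random, with baseline and post-randomization outcomes in the imputation model. The primary analysis is ANCOVA of the 8-month PEQD with baseline PEQD as covariate. No baseline-to-8-month correlation is given. No retention figure is given either, although data collection has ended.

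**The concern.** The revised power does not forecast that every family will return an 8-month PEQD. The sentence accepts that some scores will be missing and treats their imputation as equivalent to no loss. That reason is not valid. When the missing item is the primary outcome itself, imputation draws plausible values from a model fitted to the observed cases, and the variance between imputations carries the missing information into the standard error. If imputation did justify assuming no loss, the inflation from 94 to 111 per arm would have served no purpose.

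At stake is the published statement of what the primary analysis can show. The closing sentence carries no condition on SD or completeness, so a null result could be read as coming from a trial with more than 80% power whatever the number of scores observed.

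**Working it through.** **Inputs.** Difference 10 points, SD 20.8 and 5% type I error (Sample Size); 15% loss (Sample Size); 139 enrolled and alternative SD 16.7 (Results). Two assumptions are mine:
- Two-sided test. A one-sided test would need only about 75 per arm, so only two-sided fits the stated 94.
- Baseline-to-8-month correlation r = 0. The stated 94 per arm reproduces on that basis.

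**Formula.** SE = SD × √(1 − r²) × √(1/n₁ + 1/n₂); noncentrality λ = 10/SE; power from the noncentral t with N − 3 degrees of freedom (two groups, one covariate).

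**Reproducing the plan.**
- SD: (100/4 + 100/6)/2 = 20.83.
- 94 per arm: SE = 20.8 × √(2/94) = 3.03, λ = 3.30, power 90.6%. The smallest n giving 90% is 92 per arm, close to the stated 94.
- Inflation: 94/0.85 = 110.6, so 111 per arm and 222 in total.
- 139 all observed (70 + 69): SE = 20.8 × √(1/70 + 1/69) = 3.53, λ = 2.83, power 80.3%. This matches the stated 80%.

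The arithmetic is therefore sound if all 139 outcomes are observed.

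**Power when some outcomes are missing (SD 20.8, r = 0).**

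| Loss | 8-month scores observed | Power |
|---|---|---|
| 0% | 139 | 80.3% |
| about 2% | 136 | 79.5% |
| 5% | 132 | 78.3% |
| 10% | 125 | 76.0% |
| 15% | 118 | 73.5% |

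For the last row, 139 × 0.85 = 118.15; SE = 20.8 × √(2/59) = 3.83, λ = 2.61. The normal approximation gives 74.3%, so about 74%. Three missing scores (136 observed) already take power below 80%.

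**Credit for imputation.** Let n be the number observed at 8 months, n₄ the number with a 4-month score, and ρ the assumed correlation of the 4-month with the 8-month score given baseline. The effective sample size is approximately 1/[(1 − ρ²)/n + ρ²/n₄]. In a generous case, ρ = 0.7 and every family missing at 8 months has a 4-month score: 1/[0.51/118.15 + 0.49/139] = 127.5, power 76.8%. With ρ = 0.5 it is 122.8 and 75.2%; with ρ = 0 it stays at 118.15 and 73.6%. The range at 15% loss is about 74% to 77%.

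**Credit for baseline adjustment (118 observed, SD 20.8).** r = 0.3 gives 77.5%, r = 0.4 gives 80.7%, r = 0.5 gives 84.8% and r = 0.6 gives 89.9%.

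**Alternative SD of 16.7 (r = 0).** 139 observed: SE = 2.83, λ = 3.53, power 93.9%. 118 observed: SE = 3.07, λ = 3.25, power 89.7%. The article's 90% at this SD thus matches about 118 observed scores, whereas its 80% at SD 20.8 matches 139. The two scenarios appear to rest on different numbers analysed.

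**Precision (SD 20.8, r = 0).** Half-width of the 95% confidence interval: 1.98 × 3.53 = 7.0 points with 139 observed and 1.98 × 3.83 = 7.6 points with 118.

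**The case against.** The strongest defence has four parts.

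- *The change of assumption is disclosed.* This stands. A reader might infer that the Results section contradicts the Sample Size section on attrition. It does not: it says openly that it moves from 15% loss to none, and the 80% is visibly conditional on that. The fault is the reason given, and a closing sentence that drops the condition.
- *The claim of more than 80% also rests on the SD 16.7 scenario.* This stands too. Under that SD the claim holds even with 15% loss, so a reader who took it to be simply false would go too far. The scenario does not, however, repair the 80% figure given for SD 20.8, and the article cites no observed SD in its support.
- *ANCOVA will gain from the baseline PEQD.* Very likely, since the same scale is used at baseline and at 8 months. It is tempting to conclude that the trial's power is 74%. The documents do not support that as a single answer: r = 0 is only the basis on which the planned 94 reproduces, and r of about 0.4 restores 80%. Equally, the article states no correlation, so it cannot draw on one silently.
- *Retention may be better than 85%.* It may. At 5% loss the shortfall is only about 2 percentage points. The 15% is the plan's own figure, and actual retention is not reported.

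Nor should a reader conclude that imputation recovers nothing. With 4-month scores available it can recover a little, but at SD 20.8 with no baseline credit it does not bring 15% loss back to 80%.

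**Conclusion.** Wrong as written, in a limited sense. The 80% is computed correctly for 139 observed outcomes, but imputing missing outcomes does not justify assuming that none are lost. At SD 20.8, a 10-point difference, two-sided 5% and no baseline-correlation credit, 80% needs essentially all 139 scores. At the planned 15% loss power is about 74%, or up to about 77% with generous credit for the 4-month score. On that basis, and only on it, a true 10-point effect would be missed about one time in four.

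The unqualified closing claim is therefore unsupported at SD 20.8 with the planned loss unless r is about 0.4 or more. It is supported at SD 16.7. The conclusion depends on the SD, the number of scores observed and the baseline correlation; the article fixes none of these in its closing sentence.

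**What to change.** In the Results section:

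1. Remove imputation as the reason for assuming no loss to follow-up.
2. State power at the number of 8-month PEQD scores actually observed, which should be countable now that data collection has ended, or otherwise at the planned 15% loss. Give it as a conditional range: at SD 20.8, 80% with 139 observed and about 74% with 118; at SD 16.7, about 94% and 90%, all without correlation credit. Use the same number analysed for both SDs.
3. If credit for baseline adjustment is wanted, state the assumed correlation and the power that follows.
4. Qualify the closing claim of more than 80% by SD, completeness and correlation.
5. Add the expected half-width of the 95% confidence interval: about 7.6 points with 118 observed against 7.0 with 139, at SD 20.8 and r = 0.

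The cost is a reworded paragraph and a less favourable stated power. The analysis model and the missing-data method stay as they are, and no new patients or data are needed.

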## Discussion

### Expected Findings

In this study, we will evaluate the use of a patient-facing, EHR-integrated pre-clinic MyChart questionnaire in a pediatric T1D clinic as a means to improve the quality of care. We will also assess the impact of this intervention on glycemic outcomes and visit efficiency. We anticipate that our customized, intuitive patient-facing interface will increase data capture and free up time during the visit to identify and focus on priority issues, helping providers better and more efficiently support their patients. We hypothesize that this will translate into improved PREMs at 4 and 8 months in patients completing these questionnaires as compared to a control group.

Demonstrating a favorable impact of this tool and workflow would provide a rationale for this infrastructure design to be sustained in our clinic and shared with other diabetes clinics. The design can be applied to create similar EHR workflows that accommodate patient-entered data, including PREMs, into clinical documentation and care across a broad range of conditions.

### Strengths and Limitations

To our knowledge, this study will be the first randomized controlled trial to assess how caregiver-perceived quality of care is impacted by the use of a caregiver proxy-reported, EHR-integrated, preclinic questionnaire distributed via a patient portal. Methodologically rigorous research in this area is lacking, and there is a need for this to be completed and reported in sufficient detail to allow for future replication and subsequent generalizability [26-28]. Evaluation of how a patient-facing interface customized to existing workflows can help providers better and more efficiently support their patients is required to justify changes in health service infrastructure and delivery. Furthermore, patient-entered information should enhance data that exist in patients’ medical records—which, when combined and analyzed, can help to better understand differences in patient care and subsequently improve patient care and outcomes [29].

Incorporation and integration of increasingly complex patient data, personal health information, and diabetes-related information into the clinical workflow are essential for understanding our patients and optimizing care. It nonetheless poses a challenge to our resource-constrained health care system and is currently not done effectively [30]. Partnering with families to allow them to provide their own information prior to a visit, directly into their EHR in a discrete, efficient, and interpretable manner, provides an innovative way to address this challenge. Additionally, this study prioritizes the patient experience as the primary outcome, recognizing that it is a critical element in any sustained change in care models and health outcomes [12,13].

Feasibility and acceptability are important considerations for any clinical intervention. The collection of MyChart survey completion rates, as well as surveying both patients and providers involved in diabetes care, will enable further assessment of feasibility and acceptability, respectively.

There are some identified limitations to this study. The trial is not blinded, as participants, care providers, and the data analysis team could not be blinded to participant assignment groups. We also recognize the inclusion of only English-speaking participants, representing at least 85% of our patient population, and those aged under 11 years at enrollment as limitations. At our center, youth aged 12 years or older begin to control access to their patient-facing EHR account, which adds complexity related to portal use in adolescence. If favorable results ensue from this work, further study would expand the use of this tool in older age groups and address language and literacy barriers. Planned mitigation strategies for more widespread and equitable access include formal translation into the most commonly spoken non-English languages in our clinical population, with professional translation services to ensure linguistic appropriateness. We also plan to conduct language-specific usability and readability testing prior to broader implementation. Caregiver feedback provided in this study will also be used to further optimize future iterations. Furthermore, with respect to generalizability, we note that the use of electronic means of administering a patient-facing questionnaire may be a barrier [31]. Measures such as tablet access in the waiting room in advance of patient clinic appointments should be considered to optimize inclusivity. Continued efforts to ensure that electronic means of health care provision are readily accessible are paramount to avoid further exacerbating existing care disparities.

### Conclusions

If the use of a patient-facing, EHR-integrated preclinic MyChart questionnaire in a pediatric T1D clinic is shown to be effective, it will help inform the reorganization of care delivery and has the potential to impact patient outcomes beyond our institution and diabetes-specific care. It will also provide the necessary infrastructure to address longer-term diabetes-related health outcomes, to answer important quality improvement and research questions, and to increase data capture for provincial and national diabetes registries currently under development.

A diabetes flowsheet developed at our center has been adopted at a number of other Canadian pediatric centers, and if proven efficacious, we anticipate that this tool will be adopted at these other sites, further facilitating multicenter collaboration with respect to both health care delivery and diabetes research.

We are living in historic times captured by the dramatic ascendancy of diabetes technologies, virtual care, and the use of artificial intelligence in the medical realm. Diabetes is ideally suited for this new era of medicine that leverages digital solutions to improve patient care. The infrastructure built and evaluated in this study can be expanded to other populations (broadening age, language, accessibility, and conditions) and can be applied to create similar disease-specific EHR workflows that accommodate patient-entered data, including patient-reported outcome and experience measures, into clinical documentation and care provided virtually or in person. This innovation will ease our continued transition to this new virtual era across a broad range of conditions and provide a much-anticipated solution for the incorporation of PREMs into routine care.
